## 7.9 Study termination

Primary completion date will be the date that the last participant will undergo the final visit for the purpose of final collection of data for the primary outcome.

Study completion date will be the final date in which all secondary endpoints will be assessed.

## 7.10 Study and site closure

The Sponsor reserves the right to close the study site or terminate the study at any time for any reason at the sole discretion of the Sponsor. Study sites will be closed upon study completion. A study site is considered closed when all required documents and study supplies have been collected and a site closure visit has been performed. The investigator may initiate site closure at any time, provided there is reasonable cause and sufficient notice is given in advance of the intended termination.

Reasons for the early closure of a study site by the Sponsor or investigator may include, but are not limited to, the following:

• Failure of the investigator to comply with the protocol, the requirements of the IRB/EC or local health authorities, the Sponsor's procedures, or the ICH Guideline for Good Clinical Practice

• Inadequate recruitment of participants by the investigator

• Discontinuation of further study treatment development. If the study is prematurely terminated or suspended, the Sponsor shall promptly inform the investigators, the EC and the health authorities of the reason for termination or suspension. The investigator shall promptly inform the participants and should ensure appropriate participant therapy and/or follow-up.

# 8. CRITERIA FOR EVALUATION AND ENDPOINT DEFINITION

## 8.1 Primary Endpoint

The main endpoint of the study will be serum concentrations (nmol/L) of SHBG after 6 months of intervention. We expect to obtain a difference of 15 points comparing the two low dose tamoxifen arms with the two other arms that include lifestyle intervention (step counter), with or without intermittent-caloric restriction^57, 58^. The measurement will be centralized at the Division of Cancer Prevention and Genetics at the IEO.

## 8.2 Secondary Endpoints

-Change in time of SHBG, insulin, lipid profile, glucose (HOMA-index), IGF-I bioavailability (IGF-I, IGF binding proteins: IGFBP-1, -2 and -3), and Adiponectin/Leptin ratio.

-Change in quality of life (QoL) measured by MenQoL questionnaire.

-Body Mass Index, hip and waist circumference variations

-Body composition/fat distribution changes (measured by BIVA),

-Safety and toxicity (in particular for the combined intervention).

-Evaluation of differences in microbioma changes in time by arms (Tam LD vs lifestyle intervention).

- Immune-modulation by expression of inflammation cell signaling genes

In a subgroup of participants, MD and DEXA changes will be assessed.

Fasting glucose will be determined locally at each visit by the methodology adopted by each center; all other biomarkers will be measured as described in section 9.1.

In addition, quality of life will be assessed by a self-administered Quality of Life questionnaire (MenQoL); moreover, safety and toxicity will be evaluated at the clinical visit according to the Common Terminology Criteria for Adverse Events v5.0 (CTCAE).

Body composition will be evaluated by the raw bioelectrical impedance parameters by the bioelectrical impedance vector analysis (BIVA). The specific BIVA approach represents a suitable method for evaluating FM% and its changes following a lifestyle intervention program. In particular, vector displacements towards the lower pole of an R-Xc graph were found to reflect decreases in FM% after an intervention program aimed to reduce body fat. BIVA for body composition analysis will be provided to each study center.

Depending on local availability and/or women acceptance, body composition will be assessed also by patient’s DEXA according to bi-compartmental (fat mass and fat-free mass) or three-compartmental (fat mass, lean soft tissue, and bone mineral content) models. Participants will be invited to perform a DEXA at baseline and after 6 months.

Moreover, mammography breast density will be performed in a subgroup of participants (not all the participants will undergo mammography due to younger age).; the volumetric breast density from digital mammograms will be evaluated centrally (at the IEO) by the use of the Volpara software.

# 9. Collection and Handling Procedures

We will collect and process serum, whole blood and stool for evaluation of biomarkers. Specific instructions about specimen handling and storage will be provided in a separate Manual of Operations and Procedures. Storage of serum and blood samples will be centralized at the Laboratory of the Division of Cancer Prevention and Genetics, IEO, Milan. They will provide kits for sample collection and check sample identification at arrival and coordinate the shipment of samples to the specific laboratories involved in biomarker measurements.

## 9.1. Blood

Blood samples for serum biomarkers will be collected at baseline, three and six months, whole blood (EDTA) will be collected only at baseline, whole blood for RNA samples will be collected at baseline and six months.

Blood samples for biomarkers will be drawn under fasting condition (at least 6 hours) preferably between 8 a.m. and 10 a.m. at each visit. A total of 25 ml of blood (5 x 5mL) will be collected into vacuum blood collection tubes containing beads coated with clotting activator for serum separation to be employed for circulating biomarker analysis. Based on specific tubes adopted locally, reference to the manufacture instructions will be followed. blood will be allowed to clot at room temperature for 30 minutes. Then, it will be spun in centrifuge for 10 minutes. Sarstedt Serum Monovettes tubes require 10 min centrifugation at 2000 x g at room temperature, while BD Vacutainer® SST™ and PST™ gel tubes should be spun at a speed of 1300 x g. Swing-out buckets best option for both systems. After centrifugation, the yellow top layer, which corresponds to serum, is pipetted using the disposable transfer pipettes in 6 even aliquots (about 2 mL each) into the polypropylene cryotubes (Thermo Fisher Scientific), specifically labeled according to the Instructions in the Manual of Operations and Procedures. Tubes are tightly capped and stored in a dedicated – 80°C freezer equipped with a temperature control and temperature log chart or an alarm monitoring system per institutional standards.

Moreover, **3 ml whole blood** will be collected in tubes containing EDTA-K2 as anti-coagulant agent. The tube is gently mixed and blood is pipetted using disposable transfer pipettes in 2 even aliquots (about 1.5 mL each) into the polypropylene cryotubes (Thermo Fisher Scientific), specifically labeled according to the Instructions in the Manual of Operations and Procedures. Tubes are tightly capped and stored in a dedicated –80°C freezer equipped with a temperature control and temperature log chart or an alarm monitoring system per institutional standards.

Additionally, **2.5 mL whole blood** will be drawn into PAXgene® Blood RNA Tubes, for immediate stabilization of intracellular RNA, and stored at -20°C to -80°C.

**Specimen collection kits** for storage of serum and blood samples will be provided by the Central Laboratory, at the Division of Cancer Prevention and Genetics, European Institute of Oncology in Milan, Italy (See the Instructions in the Manual of Operations and Procedures for requesting kits). Briefly, they will provide labels and polypropylene cryotubes and rack (Thermo Fisher Scientific) and instructions for specimen handling, processing, labeling, tracking and storage.

Each local site must be equipped with a -80°C (range -70 °C to -80 °C) freezer provided with temperature control 24 hours a day, 7 days a week and temperature log charts or an alarm monitoring system, better if electronic. The center should also be equipped with a back-up freezer.

## 9.2 Stool

Fecal samples will be collected for microbiome analysis at baseline and final visit. Specimens will be collected by patients at home and transported in a collection tube prefilled with preservative liquid, which stabilizes nucleic acids preventing them from being degraded up to 6-8 weeks at room temperature.

Specimen collection kits for storage of fecal samples will be provided by the European Institute of Oncology in Milan.

## 9.3 Biomarkers Methods

**Sex hormone binding globulin (SHBG)**

Serum concentrations of SHBG will be determined by a chemiluminescent immunoassay designed for the IDS-iSYS Multi-Discipline Automated System (Immunodiagnostic Systems Limited, United Kingdom). Lower Limit of Quantitation is 0.30 nmol/L.

**Insulin and lipids**

Serum concentrations of insulin will be determined by a chemiluminescent microparticle immunoassay (CMIA) on the ALINITY *i* System (Abbott Laboratories, Weisbaden, Germany). This assay shows very good agreement with our previously adopted platforms and the assay performance in terms of reproducibility were improved. The sensitivity of the method is ≤ 1.0 μU/mL, and inter-assay coefficient of variation are below 2% at 3 different control levels (low, median, high) produced by Abbott. Inter-assay coefficient of variation of our in-house prepared serum pool (mean: 4.9 μU/mL) is 3.9%. Additionally, we will measure total, LDL, HDL cholesterol and triglycerides levels by the same method.

**HOMA-index**

We will calculate the HOMA index, i.e. [fasting insulinemia (mU/L) x glycemia (mmol/L)]/22.5, to be applied as a surrogate index of insulin resistance.

**Adiponectin and leptin**

Serum adiponectin, leptin and cytokines (IL-6 TNF-alpha) will be measured using an automated platform for immunoassays (ELLA system, ProteinSimple). ELLA is a platform based on a microfluidic technology, that allows to perform automated immunoassays without manual steps in 72 minutes. The inter-assay CVs for adiponectin QCs and our internal control are 4.98% and 6.62%. The inter-assay CVs for leptin QCs and our internal control are 6.77% and 5.35%. The inter-assay CVs of our pooled serum for IL-6 and TNF-alpha were 5.4% (mean 1.26 pg/mL) and 4.6 % (mean 6.89 pg/mL), respectively

**Insulin like growth factor I (IGF-I) and IGF binding protein 3 (IGFBP-3)**

Serum concentrations of IGF-I and IGFBP-3 will be measured by means of commercially available assays, intended for the quantitative determination in human serum or plasma on the IDS-iSYS Multi-Discipline Automated System. Serum samples from the same participants obtained at different time-points will be run in batches in order to reduce analytical variability. Standards for good laboratory practice are applied. Monitoring of precision and reproducibility will be performed by processing commercially available control samples and internal in-house prepared pool of samples in each run.

**Insulin like growth factor binding protein 1 (IGFBP-1) and IGFBP-2**

IGFBP1 and IGFBP-2 will be measured by the Human ELISA (Enzyme-Linked Immunosorbent Assay) kit is an in vitro enzyme-linked immunosorbent assay purchased from Abcam Cambridge, UK.

**hsCRP (high sensitive C-reactive protein)**

We will measure serum concentrations of C-reactive protein by a high sensitivity turbidimetric method according to the manufacturer’s instructions (Roche Diagnostics, Mannheim, Germany). The test is designed for the automated instrument COBAS INTEGRA 800. Sensitivity for the hsCRP assay is 0.1 mg/L and the intra- and inter-assay coefficients of variation are expected to be 4.1% and 6.4%, respectively for a control sample of 0.423 mg/L.

**Immune Responses - Gene expression profile**

RNA will be extracted by Qiagen Kit, then subjected to reverse transcription reaction using RT2 first strand kit (Qiagen). Real-Time qPCR performed in triplicate using RT2 Profiler PCR Array (RT² Profiler- PCR Human Innate & Adaptive Immune Responses, Qiagen) for expression of inflammation cell signaling genes. Plates will be run on ViiA7 (Applied Biosystems 384 well blocks), according to standard PCR protocols and online software (http://pcrdataanalysis.sabiosciences.com/pcr/arrayanalysis.php, Qiagen). Cell signalling pathway using CellFate algorithm.

**Microbiome**

Microbial genomic DNA will be extracted from frozen samples using DNeasy PowerSoil Pro Kit (Qiagen) according to the manufacturer’s instructions, then DNA will be quantified using a Bioanalyzer (Agilent Technologies, CA) and the V3-V4 hypervariable regions of the bacterial 16S rRNA gene will be sequenced on a MiSeq platform (Illumina), 26 enabling taxonomic identification. The 250 bp 16S reads will be processed through QIIME2 (version 2019.7)^59^ as follows: (1) Following visualization of demultiplexed samples and the average quality across the reads, quality filtering, dereplicating, and chimera filtering will be performed using the DADA2^60^ plugin within QIIME2, setting the truncation length at 250 bp and the trimming by the length of the V3-V4 primer sequences (--p-trunc-len-f 250, --p-trunc-len-r 250, --p-trim-left-f 17, --p-trim-left-r 2, --p-trunc-q 2), and using consensus as the chimera filtering method; (2) a phylogenetic tree will be generated for downstream core diversity analyses using SATe’-enabled phylogenetic placement (SEPP)^61^, which first generates a reference tree—in this case using the SILVA 128 database^62^ then inserts 16S sequence fragments into the tree, thus achieving accuracy in phylogenetic tree reconstruction while retaining as much sub-OTU sequences as possible in the tree alpha and beta diversity core metrics will be determined using the qiime diversity command, with the rarefaction depth set to the minimum sequence read output across the samples, after which statistical group comparisons of alpha and beta diversity metrics will be performed, using Kruskal-Wallis for alpha diversity and PERMANOVA for beta diversity; taxonomy classification will be performed using the QIIME feature-classifier classify-sklearn feature, using a Naïve Bayes classifier trained on SILVA 132 99% OTUs full-length 16S rRNA sequences^62^, available from the QIIME2 website (https://docs.qiime2.org/2018.11/data-resources/). After filtering the feature count table for unassigned reads and setting a prevalence filter of >50% of the samples, the tables will be collapsed to each taxonomic level (kingdom, phylum, class, order, family, genus, species) and will be exported for further analysis in R. Differential abundance analysis will be performed on the raw counts table using DESeq2^63^, Statistical significance of log2 fold changes will be assessed using the default Wald test with Benjamin-Hochberg p-value correction in DESeq2. Cut-off for all significance tests was set at P < 0.05. Amplicon-based metagenomic approach represents one of the best strategies to obtain a largescale assessment of the taxonomic content of complex samples while containing costs.

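### Section 9.3 says reads are trimmed by primer length but sets the reverse trim to 2 bases, which cannot be a primer length

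*Protocol*

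**What the plan says.** Protocol section 9.3, under Microbiome, describes sequencing of the V3-V4 region and then the processing: "The 250 bp 16S reads will be processed through QIIME2". The DADA2 step is given first as a rule in words, "the trimming by the length of the V3-V4 primer sequences", and then as command settings in brackets. Truncation is "p-trunc-len-f 250, --p-trunc-len-r 250". The forward trim is "p-trim-left-f 17", and the reverse trim that follows it is 2. Rule and settings stand together in one sentence: "trimming by the length of the V3-V4 primer sequences (--p-trunc-len-f 250, --p-trunc-len-r 250, --p-trim-left-f 17, --p-trim-left-r 2".

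The section does not name the primers or give their lengths. It describes no other primer-removal step before or after DADA2.

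The output feeds a phylogenetic tree, diversity metrics compared "using Kruskal-Wallis for alpha diversity and PERMANOVA for beta diversity", taxonomic classification and differential abundance testing. Section 8.2 lists the endpoint this serves: "Evaluation of differences in microbioma changes in time by arms". Section 12.3 uses taxon abundances in further models.

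**The concern.** The rule speaks of primer sequences in the plural, so both trims should equal a primer length. The forward value can. The reverse value cannot, whichever primer is used. The 17-base forward trim also implies that primers are still on the reads when DADA2 starts, so the reverse primer is presumably there too.

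Primer bases come from the synthetic oligonucleotide and not from the organism. If the primer is made with mixed bases at some positions, copies of one organism's sequence can differ there for no biological reason. DADA2 separates sequences on single-base differences, so it can report these copies as distinct variants, and chimera filtering can be affected as well. At stake is the quality of the variant table behind a stated secondary endpoint.

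**Working it through.** **Inputs from section 9.3.** Read length 250; truncation 250 for both reads; forward trim 17; reverse trim 2.

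**Input not in the protocol.** The reverse primer length L. It is assumed to lie between 15 and 25 bases, with the protocol's own forward value of 17 as a reference point.

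**Step 1, what the settings keep.** Bases kept = truncation length − trim.
- Forward: 250 − 17 = 233.
- Reverse: 250 − 2 = 248.

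**Step 2, does the reverse value obey the rule?** The rule requires the reverse trim to equal L. A trim of 2 satisfies this only if L = 2, which is not a possible PCR primer. The stated value therefore cannot be reproduced from the stated rule.

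**Step 3, primer left in each reverse read.** Bases left = L − 2; share left = (L − 2)/L; bases kept once the rule is followed = 250 − L.

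| Assumed L | Primer bases left | Share of primer left | Reverse bases kept if trim = L |
| --- | --- | --- | --- |
| 15 | 13 | 86.7% | 235 |
| 17 | 15 | 88.2% | 233 |
| 20 | 18 | 90.0% | 230 |
| 21 | 19 | 90.5% | 229 |
| 25 | 23 | 92.0% | 225 |

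Most of the reverse primer remains at every assumed length, so this result does not depend on the exact L.

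**Step 4, how many samples.** Section 7.1 schedules stool at T1 and T6. Section 12.1 plans 200 women with 10% drop-out, leaving 180. Samples number 2 × 180 = 360 if only completers count, 200 + 180 = 380 if drop-outs give a baseline sample only, and at most 2 × 200 = 400. All would pass through the same setting.

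**Step 5, why the consequence cannot be sized.** If the residual primer held k positions each with three possible bases, one true sequence could appear as at most 3^k variants: 1 for k = 0, 3 for k = 1, 9 for k = 2. The protocol does not give k, and k = 0 means no splitting at all. The figure is a conditional ceiling on variants, not an effect on any trial result.

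**The case against.** The strongest reply is that this is a clerical slip. The rule in words is clear, a digit may have been lost in typing or in file conversion, and a laboratory that follows the words would trim correctly. That is plausible, and a look at the source file or the laboratory's command script would settle it. It does not remove the point: the protocol fixes an executable value that breaks its own rule, and nothing in section 9.3 tells the analyst which of the two governs.

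The reply is stronger on consequences. A reader might infer that richness will be inflated, that real variants will fall below the >50% prevalence filter, that every later microbiome analysis is spoiled, or that the comparison of arms is biased. The documents support none of these:

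- **Richness.** Inflation depends on mixed-base positions that the protocol does not describe.
- **Prevalence filter.** Section 9.3 applies it before aggregating to taxonomic ranks, so a loss is possible. But every sample would share the same primer mixture, so split variants of an abundant organism would tend to recur across samples and pass. No loss can be quantified.
- **Later analyses.** Surviving variants that differ only in primer bases would normally be classified alike and merged again on aggregation, and section 12.3 works largely on taxa. In the phylogenetic tree, near-identical sequences would sit close together. The main exposure is diversity measures that count each variant as distinct.
- **Bias between arms.** The same setting applies to all arms and both time points, so the error is non-differential.

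It is also fair that raw reads can be reprocessed, and that section 12.1 calls the secondary objectives explorative.

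**Conclusion.** The point holds as an internal contradiction in section 9.3: a reverse trim of 2 cannot be the length of a primer. Run as written, about 13 to 23 primer bases, or 87% to 92% of the reverse primer, would stay in every reverse read. That rests on two assumptions: a reverse primer of 15 to 25 bases, and no primer removal outside the steps the protocol describes.

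The further effect is conditional. If the primer has mixed-base positions, spurious variants and disturbed chimera filtering can add noise, chiefly to variant-level alpha and beta diversity. Its size cannot be computed from the protocol. It is the same in all arms and partly offset by taxonomic aggregation. The primary SHBG endpoint and the sample size of 200 are unaffected. The value should be corrected, but it does not threaten the trial's main conclusion.

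**What to change.** Confirm with the sequencing laboratory which primer pair is used. State both primer lengths in section 9.3 and set `--p-trim-left-r` to the full length of the reverse primer. Alternatively, remove both primers by sequence match before DADA2 and describe that step instead of the fixed trims. If primers are in fact removed earlier, say so and reconcile both trim values with that.

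The cost is one corrected value and a line of text, with no new data or samples. The added trim comes off the primer end of the reverse read, not the far end where paired reads overlap. Reprocessing after a first run is possible, but correcting the value beforehand avoids a change that could look like a post-hoc choice.

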## 1.2 Secondary Objectives

The secondary aims are:

-to verify whether ICR significantly modulates main and secondary endpoints such as HOMA-index, immune and inflammatory markers, lipid profile, Adiponectin/Leptin (A/L) ratio, quality of life (QoL), Body mass index (BMI), fat body composition, safety and toxicity;

-to verify whether LDT significantly modulates secondary endpoints, such as HOMA-index, immune and inflammatory markers, lipid profile, A/L ratio, QoL, BMI, fat body composition, safety and toxicity;

-to investigate differences in microbiome composition by arms and the effect of changes in microbiome on QoL taking into account circulating biomarkers, cytokines, immune modulators and inflammatory proteins in serum;

- to investigate MD (Mammographic Breast Density) changes by LDT vs LI, with or without ICR. This aim will be performed in a subgroup of participants (not all the participants will undergo mammography due to younger age).

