To limit the risk of technical bias and take into account the compositional nature of microbiome data, the normalized taxa abundances will be first transformed with the Centred Log-Ratio (CLR) transformation. The most discriminative taxa associated with treatment arms will be selected by using variable selection approaches adapted for compositional data, like Sparse Least Square – Discriminant Analysis (sPLS-DA) and Coda-LASSO. Multivariate linear regression models will be performed to estimate the association between Tamoxifen, LI, ICR and post-treatment clr-abundances of taxa, adjusting for confounders. Associations between post-treatment taxa and consumption of specific groups of foods will be also investigated. The level of physical activity will be quantified with the IPAQ questionnaire. Three categories of physical activity (Low, Moderate, High) will be calculated for each patient following the IPAQ scoring protocol^66^. For QoL assessment, we will analyze the four domains of MenQoL questionnaire: vasomotor, psychosocial, physical and sexual. The overall score of each domain will be calculated by dividing the sum of the domain’s items by the number of items within that domain. Higher domain scores will indicate worse QoL. Associations of the four domains with treatment, LI, ICR and taxa abundances will be estimated considering both post-treatment evaluations (at 3 months and 6 months) and changes from baseline. Multivariate linear or logistic regression will be implemented according to whether the four domains will be analyzed as continuous scales or categorized into classes. The interplay among treatment, serum biomarkers, species (normalized data) associated with treatment arms, diet and QoL will be investigated first with unsupervised methods, like networks based on Spearman’s rank Correlation Coefficient and Canonical Correspondence Analysis (CCA), then with supervised methods for data integration, like block Sparse Least Square-Discriminant Analysis (sPLS-DA) and priority-LASSO hierarchical approaches. To estimate the role of *microbiome* as mediator of treatment arms on SHBG and other biomarkers changes and to investigate its role in mediating the effect of treatments on side effects and QoL, we will perform a mediation analysis based on a counterfactual framework approach. The microbial composition of each patient will be summarized with methods of dimensionality reduction like Principal Component Analysis (PCAPathways data will be preprocessed and analyzed as described for the taxonomic data.

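### The microbiome endpoint is change by arm in paired stool samples, but the named diversity and taxon analyses do not use the baseline sample, which costs power

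*Protocol*

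**What the plan says.** Section 8.2 lists as a secondary endpoint "Evaluation of differences in microbioma changes in time by arms (Tam LD vs lifestyle intervention"). The Schema likewise places microbiome composition among the endpoints measured as changes over time. The objective in section 1.2 is looser and does not mention change: "to investigate differences in microbiome composition by arms".

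The design supplies the data for a change analysis. Section 9.2 states: "Fecal samples will be collected for microbiome analysis at baseline and final visit".

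The analyses are named in two places.

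- **Section 9.3, Microbiome.** For diversity: "statistical group comparisons of alpha and beta diversity metrics will be performed, using Kruskal-Wallis for alpha diversity and PERMANOVA for beta diversity". For differential abundance: "Statistical significance of log2 fold changes will be assessed using the default Wald test with Benjamin-Hochberg p-value correction in DESeq2". The threshold is also fixed: "Cut-off for all significance tests was set at P < 0.05". The text does not say what the groups are, which visit enters, or how a woman's two samples are linked.
- **Section 12.3.** For taxa: "Multivariate linear regression models will be performed to estimate the association between Tamoxifen, LI, ICR and post-treatment clr-abundances of taxa, adjusting for confounders". No diversity test is given. The same section names changes from baseline for the serum biomarkers and for the MenQoL domains, but not for taxa or diversity.

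**The concern.** The endpoint is a comparison of within-woman change, and a baseline stool sample is collected from every woman to support it. None of the named diversity or taxon analyses is said to use that sample. Kruskal-Wallis and PERMANOVA, as plain group comparisons, have no term for baseline or for the woman, and the section 12.3 regression has the post-treatment abundance as its outcome.

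Gut diversity is likely to differ between women in ways that persist from one visit to the next. If baseline is left out, that stable variation stays in the error term and a real difference between LDT and LI is harder to detect. If Kruskal-Wallis is run across all four arms, more power goes to contrasts that the endpoint does not ask about.

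**Working it through.** **Inputs from the protocol.** Section 12.1 gives 180 evaluable women, 90 per pooled group, and 200 enrolled with 10% drop-out. Section 9.3 gives the 0.05 cut-off. Section 9.2 gives two stool samples per woman.

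**Assumptions, because the protocol gives no figure.** The effect is 0.3 SD on an alpha-diversity metric with SD 1 at each visit. The within-woman correlation r between baseline and month 6 runs from 0.3 to 0.9. The 10% drop-out is taken to apply to stool as well.

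**The plan's own figure.** No power is stated for the microbiome. The only sample-size figure is for SHBG: difference 15, SD 35, 90 per group. It reproduces, with t-test power 81.6% against 80% stated and 180 / 0.9 = 200. So 90 v 90 is a fair basis here.

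**Step 1: two-group power.** Power = Phi(0.3 x sqrt(90/2) / s - 1.96), where 0.3 x sqrt(45) = 2.012 and s depends on the analysis:

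- month 6 only: s = 1
- change score: s = sqrt(2(1 - r))
- month 6 adjusted for baseline: s = sqrt(1 - r^2)

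| r | Month 6 only | Change score | Baseline-adjusted |
|---|---|---|---|
| 0.3 | 52% | 40% | 56% |
| 0.5 | 52% | 52% | 64% |
| 0.7 | 52% | 74% | 80% |

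Worked line at r = 0.5: s = sqrt(0.75) = 0.866; 2.012 / 0.866 = 2.324; Phi(2.324 - 1.96) = Phi(0.364) = 64%.

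Simulation with Kruskal-Wallis on month 6 gave 48-51%. Simulated baseline-adjusted power was 54%, 64% and 80% at r = 0.3, 0.5 and 0.7. Put as sample size, baseline adjustment with 90 women per group is worth 90 / (1 - r^2) women per group without it: 99, 120 and 176 at these three correlations.

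**Step 2: four-arm omnibus test.** With 45 women per arm and the same 0.3 SD effect in both LDT arms, Kruskal-Wallis on month 6 rejected in about 32-34% of simulated trials. The drop from about 50% comes from spending three degrees of freedom on a one-degree-of-freedom question. It is separate from the baseline issue.

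**Step 3: Type I error by what enters the test.**

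- Month 6 only, by arm: simulated 4.7-5.0% with two groups, so no inflation.
- Within-woman change, by arm: simulated 4.5-5.2% with two groups, so no inflation.
- Both visits pooled by arm as if independent: 2 x (1 - Phi(1.96 / sqrt(1 + r))) = 8.6%, 11.0%, 13.3% and 15.5% at r = 0.3, 0.5, 0.7 and 0.9. Simulation gave 8.6%, 11.8%, 12.6% and 15.0%.

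The third case is shown only to bound the risk. The protocol does not describe it.

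**The case against.** The strongest reply is that nothing named is invalid. Randomisation makes the arms equal in expectation at baseline, so a month-6 comparison targets the same expected arm effect as a comparison of change, and it holds 5%. Section 12.3 points to that reading by modelling post-treatment abundance, one sample per woman, and the section 1.2 objective speaks of composition rather than change. This stands: what is lost is power, not validity.

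It can also be said that which visit enters, the DESeq2 design and the permutation scheme belong in a statistical analysis plan, which is not at hand. That is fair as far as it goes, and their absence is not the point. Section 9.3 does fix Kruskal-Wallis and PERMANOVA as group comparisons, and a better analysis is available from a sample already collected. Adjustment for confounders in section 12.3 might be taken to cover baseline abundance, but the text does not say so.

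Three stronger readings are tempting and not supported.

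- **That the plan produces false positives.** This needs both visits to be pooled as independent samples, and the protocol never says that.
- **That Kruskal-Wallis cannot test the endpoint.** Applied to each woman's change in alpha diversity it would be valid. Section 9.3 simply does not say that change is what enters.
- **That the DESeq2 analysis ignores pairing.** "Statistical significance of log2 fold changes will be assessed using the default Wald test" names the test statistic, not the design formula, so a woman, baseline or arm-by-time term is not excluded.

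The size of the gain also depends on r. At 0.3, baseline adjustment adds only about 4 points, and a change-score test would lose 12.

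**Conclusion.** The point holds as one of efficiency and consistency. Section 8.2 asks about change by arm in paired samples, while the analyses named in sections 9.3 and 12.3 do not use the baseline sample or the pairing.

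If month 6 alone is compared, the error rate is correct. For 0.3 SD at 90 v 90, the power given up against a baseline-adjusted analysis is about 4, 12 and 28 points at r = 0.3, 0.5 and 0.7. A four-arm omnibus test would lower month-6 power further, to about 33%. These figures rest on an assumed effect size and assumed correlations, approximately normal metrics, and complete pairs in 90 women per group. They were worked for alpha diversity and are only indicative for taxa and beta diversity.

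The microbiome endpoint is secondary, and section 12.1 treats the secondary objectives as exploratory. The SHBG primary analysis is untouched.

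**What to change.** Amend sections 9.3 and 12.3 so that the analyses match section 8.2, with the woman as the unit.

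- **Alpha diversity.** Replace Kruskal-Wallis with a linear model of month-6 diversity on baseline diversity, LDT v LI, ICR and the stratification factors (center and disease status). Test LDT v LI as a single-degree-of-freedom contrast. Prefer this to a change-score test, which gains nothing over month 6 alone at r = 0.5 or below.
- **Beta diversity.** Use PERMANOVA of the arm-by-time term, permuting whole women so that each woman's two samples stay together. Alternatively, state that only month 6 enters, with one sample per woman.
- **Taxa.** Add baseline CLR abundance to the section 12.3 regression. If both visits enter DESeq2, specify an arm-by-time term with women nested in arm. The Wald test can stay.

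The cost is protocol wording and a few lines of code, with no added samples, visits or participants. The one drawback is that women without both stool samples contribute less to the paired or adjusted analyses.
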